| STUDY OUTLINE             | 
Mothers and their infants from the region of Berlin, Groningen, Milan, Naples and Zurich will be approached in the first 8 weeks of the infant's age to participate in the study if they fulfil all inclusion but not exclusion criteria. Participation in the study will be voluntary and written informed consent will be obtained.
 
Mothers who cannot/do not fully breastfeed their infants and have fed their infant at least one bottle of standard (non-hydrolysed) cow's milk based formula will be asked to be randomised to one of the two formula groups. The formulas (IF/ FOF) will be used until the infants reach 1 year of age. Mothers fully breastfeeding their infant at study entry are asked to join the reference group.
 
At inclusion (examination day 1), questionnaires will be filled in with data on the mother incl. age, demography and socio-economic status, occupation, general health, nutritional status, delivery etc. Furthermore, the infants will be clinically examined and data on their feeding pattern and health status collected (basal questionnaire). A stool sample will be taken before the study feeding starts.
 
The mothers will be issued with a diary supporting the collection of data on feeding pattern, occurrence of any symptoms of illness etc. afterwards.
 
There are 4 further examination days planned with personal contacts (visits at clinic or at home) at the infant's age 2, 4, 6, and 12 months, at which the clinical examinations incl. anthropometry will be repeated and again data on feeding pattern and health status (follow-on questionnaire) as well as a stool sample will be collected. Acceptance and tolerance of the study feeding regimens as well the occurrence of allergic symptoms (atopic dermatitis) will also be checked.
 
If the mother gave her written informed consent at study entry that the child may provide two blood samples (2-3 ml), i.e. at the infant's age of 6 and 12 months, a respective blood sample will be collected at the examination days 4 and 5.
 
In between the examination days with personal contacts to the mothers and their infants, there are structured interviews planned, during which the parents are asked about the health status of their infant (occurrence of fever, other symptoms of illness, use of medication etc.), the feeding pattern incl. acceptance and tolerance, possible complaints, etc. (follow-on questionnaire).
 
The combination of 5 major visits in the clinic/at home and regular intermittent contacts (home visits, telephone calls) will guarantee contacts to the mothers in 2-4 weekly intervals (2 weekly till the infant's age of 4 months, 4 weekly afterwards). This will enhance study adherence and allows the cross-check of the questionnaires.
 
If any illness of the infants will require a visit to the clinics/practitioners, illness related details should also be collected for later evaluation (diagnoses, medication etc.).
 |

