### **12.3 Per-protocol- and intention-to-treat-analysis**

The protocol foresees for the formula infants that they reach full formula feeding (FF) after 2 months of age at the latest and for the reference infants that they should stay on full breastfeeding (BF) for at least 4 months. Formula infants should cover all formula feedings during the study duration, i.e. till the infant's age of one year, with study IF/FOF. Deviations from this protocol will result in exclusion from the defined formula and breastfed groups with respect to the intended per-protocol-analysis (PP) after the study's end. Formula infants receiving breast milk beyond the age of two months will be evaluated in the per-protocol analysis as members of a mixed-feeding group (duration and estimated amount of breast milk intake will be recorded and statistically checked). For the intention-to-treat analysis (ITT), all infants having been randomised will be evaluated according to the initial group allocation.

[figure not shown]

## 12.4 Examination day 1

The most important examinations will be performed at 5 examination days throughout the study. Day of study entry is defined as *examination day 1*. Questionnaires will be filled in with data on the mother incl. age, demography and socio-economic status, occupation, general health, nutritional status, delivery etc. Data on the feeding pattern will be collected as well (basal questionnaire). The clinical examination of the infant will include anthropometry but to check for pre-existing illnesses which might interfere with the study also the assessment of atopic dermatitis and other skin symptoms (eczema, urticaria, others) as well as the assessment of respiratory (rhinitis, wheezing, etc.), GI tract (vomiting, colics, diarrhoea) and general symptoms (failure to thrive, irritability, food refusal).

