## 12.5 Additional examinations in study subgroups

If the mother agreed that her child may provide stool samples for check of stool parameters on gut health and immune status throughout the study (examination day 2-5), faeces should be collected for later quantitative and qualitative bacterial analysis, pH measurements as well as analysis of faecal sIgA. Thus she will receive stool containers provided by NUMICO in which she should collect some fresh stool sample from her infant's first nappy of one day in the week before the next examination day (to be kept frozen and to be delivered by the mothers at next examination day). If the mother agreed that her child may also provide two times a small blood sample (2-3 ml) for more direct check of the immune status, a blood sample should be drawn for later analysis of biochemical blood/plasma parameters at the infant's age of 6 and 12 months. If infants are seriously ill or feverish at the time of the blood sampling or if they used antibiotics in the 2 weeks preceding the blood sampling (as indicated by the parents or concluded from the anamnesis), the sampling point can be postponed for up to 2 weeks.

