**12.12 Study schedule overview**

The planned schedule is depicted in the following table.

| Age of infant (w)               | 0 - <8   | 8      | 10 | 12    | 14 | 16     | 18 | 20    | 22 | 24     | 26 | 28    |
|---------------------------------------------|----------|--------|----|-------|----|--------|----|-------|----|--------|----|-------|
| Personal contact (clinic / home visit)      | X (U2/3) | X      |    |       |    | X (U4) |    |       |    | X (U5) |    |       |
| Interview (home visit or telephone contact) |          |        | X  | X     | X  |        |    | X     |    |        |    | X     |
| Examination day                             | 1        | 2      |    |       |    | 3      |    |       |    | 4      |    |       |
| Informed consent                            | X        |        |    |       |    |        |    |       |    |        |    |       |
| Randomization                   | X        |        |    |       |    |        |    |       |    |        |    |       |
| Clinical examin.                            | X        | X      |    |       |    | X      |    |       |    | X      |    |       |
| Basal questionnaire                         | X        |        |    |       |    |        |    |       |    |        |    |       |
| Follow-on quest.                            |          | X      | X  | X     | X  | X      |    | X     |    | X      |    | X     |
| General assessment by the PI                |          |        |    |       |    | X      |    |       |    | X      |    |       |
| Special recheck of feeding group            |          | X (FF) |    |       |    | X (BF) |    |       |    |        |    |       |
| Vaccination with HEXAVAC        |          | D      |    | I; D  |    | D      |    | I     |    |        |    |       |
| Stool sample                    |          | X      |    |       |    | X      |    |       |    | X      |    |       |
| Blood sample                    |          |        |    |       |    |        |    |       |    | X      |    |       |
| Formula provided                | IF       | IF     |    | IF    |    | IF     |    | IF    |    | FOF    |    | (FOF) |
| Age of infant (w)               | 30       | 32     | 34 | 36    | 38 | 40     | 42 | 44    | 46 | 48     | 50 | 52    |

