### **13.3 Faecal parameters (secondary outcome parameter)**

For each examination day, a stool sample of approximately 2-5 g faeces will be collected into stool containers provided by NUMICO Research and stored at -20°C for later analysis. The microbial composition of the faecal samples will be tested in those samples in selected subgroups directly by fluorescent in situ hybridisation (FISH) using specific 16S rRNA-targeted oligonucleotide probes for e.g. *Bifidobacteria*, *Lactobacilli*, *Bacteroides*, *E. coli* and *Clostridia*. Amounts are expressed as percentage of the total number of bacteria. FISH analyses will be organised by NUMICO Research.

As further faecal parameters of gut health and immune status, faecal pH will be measured and faecal antibodies (sIgA) determined with standard laboratory techniques (Elisa, FACS, RT-PCR).

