### **14.3.1 Interval data**

Inter-group comparisons will be performed for all interval data at any measurement point by using the analysis of variance (ANOVA) / T-test (if necessary to perform non-parametric tests -> Kruskal-Wallis test / Wilcoxon-Mann-Whitney U-test). In case of significance of the multiple group comparison, single group comparisons will be performed as post-hoc tests according to Fisher (if necessary to perform non-parametric tests -> Wilcoxon-Mann-Whitney-U-test).

For baseline adjustment, comparisons will be calculated not only using the raw data but also data differences (e.g. data at examination day 2 and 3 minus data at examination day 1) to account for individual variances.

Whenever needed, logarithmic transformation of data will be performed for homogenisation of variances prior to statistical analysis.

Within-group comparisons (e.g. examination day 3 versus day 1) will be conducted using the paired T-test (if necessary to perform non-parametric tests -> Wilcoxon-signed rank test).

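### The protocol gives two incompatible stool schedules, so sites following sections 12.4, 12.5, 12.7 and 12.12 would lack the pre-feeding sample that the day-1 differences in 14.3.1 need

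*Protocol*

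**What the plan says.** Two places require a stool sample at study entry. The synopsis, under Study outline, describes inclusion as examination day 1 and states: "A stool sample will be taken before the study feeding starts". It then lists four further examination days, at 2, 4, 6 and 12 months, at which data "as well as a stool sample will be collected". Section 13.3 reads: "For each examination day, a stool sample of approximately 2-5 g faeces will be collected". The protocol has five examination days, and section 12.4 says "Day of study entry is defined as" examination day 1.

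Four places start later:
- Section 12.5 concerns "stool samples for check of stool parameters on gut health and immune status throughout the study (examination day 2-5", so day 1 is outside its range. Mothers are given containers and collect a sample in the week before the next examination day.
- Section 12.4 lists the day-1 questionnaires and clinical examination but no stool.
- Section 12.7 marks stools at examination days 2, 3, 4 and 5.
- The stool row in section 12.12 is empty in the 0 to <8 week column and marked at weeks 8, 16, 24 and 52.

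For baseline adjustment of interval data, section 14.3.1 uses raw values and also "data differences (e.g. data at examination day 2 and 3 minus data at examination day 1) to account for individual variances". Section 14.2 gives quantitative faecal flora as an example of interval data.

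**The concern.** The sections that a site works from are the day-1 procedures, the subgroup procedures, the list of later examination days and the schedule table. All of them leave out the pre-feeding stool. The sections that a laboratory or an analyst would read include it. A centre that follows the schedule faithfully would therefore not collect a value that the analysis section expects.

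The sample can be taken only once. Randomisation is immediate at entry (12.2) and study formula is handed out at entry (12.11), so after the first study feed no stool can serve as a pre-treatment baseline. Infants may enter at any age up to 8 weeks, after differing amounts of breast milk and standard formula. A baseline for flora, pH and sIgA is therefore useful both for adjustment and for checking comparability of the groups. If centres resolve the conflict differently, the baseline will be present in some and absent in others.

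**Working it through.** The point rests on cross-reading. The protocol states no figure to reproduce.

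**Stool time points by section**

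| Place | Examination days | Count |
|---|---|---|
| Synopsis, Study outline | 1 (before study feeding), then 2, 3, 4, 5 | 5 |
| 13.3 | each of the five | 5 |
| 12.4 (day-1 procedures) | no stool listed | – |
| 12.5 | 2–5 | 4 |
| 12.7 | 2, 3, 4, 5 | 4 |
| 12.12 stool row | weeks 8, 16, 24, 52 = days 2, 3, 4, 5 | 4 |

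The blank cell in 12.12 is not an artefact of reading the table, because the prose of 12.5 and 12.7 matches it. The container procedure in 12.5 matches it too: a container issued at entry for a sample before the next examination day yields its first sample for day 2.

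**Link to the analysis**

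The planned difference is (value at day 2 or 3) − (value at day 1). Under the five-point schedule both terms exist. Under the four-point schedule the second term exists for no stool variable.

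The week-8 sample is not a general substitute. Most infants entering before week 8 will already have had study formula by then, so subtracting that value would remove part of any early formula effect. Only for infants entering at about 8 weeks do days 1 and 2 nearly coincide.

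**What a baseline is worth**

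Let rho be the correlation between the day-1 value and a later value of the same stool variable, with equal variances at both times. The protocol gives no rho. I assume 0.3 to 0.6.

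- ANCOVA with the day-1 covariate: residual variance is 1 − rho² times the raw variance. At rho 0.3 this is 1 − 0.09 = 0.91, and at rho 0.6 it is 1 − 0.36 = 0.64. The reduction is rho², that is 9% and 36%.
- Change score, as in 14.3.1: variance is 2(1 − rho) times the raw variance. At rho 0.3 this is 2 × 0.7 = 1.4, and at rho 0.6 it is 2 × 0.4 = 0.8. The change score is more precise than the raw comparison only when 2(1 − rho) < 1, that is rho > 0.5.

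The 9% to 36% therefore belongs to covariate adjustment. At the lower end of the assumed range, the change score is 40% more variable than the raw value.

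**The case against.** A reader might infer that no baseline stool will exist and that the adjusted analysis of faecal outcomes is impossible. The documents do not support that. The synopsis and 13.3 expressly require the sample, and a site following them would have it. The differences are unobtainable only where 12.5 and the schedule are followed.

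The day-1 subtraction in 14.3.1 is an example for interval data in general and names no faecal variable. It works as written for anthropometry, which is measured at study entry (13.6). It reaches stool data through the section's scope of all interval data and through 14.2. That link is sound, but the differences come in addition to the raw comparison and do not replace it. Faecal parameters are also secondary outcomes in consenting subgroups.

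A reader might also infer that a baseline missing in some centres would bias the formula comparison. Randomisation is stratified by centre in blocks of four (10.4), so missingness that follows the centre affects both formula groups alike. It costs precision and would not by itself introduce bias. Nor does the protocol show that centres would in fact diverge; that is a risk created by the text.

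Finally, a one-word change to 12.5 would not be enough, because its container procedure cannot produce a day-1 sample. All these limits stand. The contradiction between the two schedules remains.

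**Conclusion.** The concern holds as an inconsistency that must be reconciled. Two places require a day-1 stool, three start collection at day 2, and the list of day-1 procedures contains none. Where the operational sections are followed, the day-1 differences planned in 14.3.1 cannot be calculated for faecal outcomes, and the loss is permanent for every infant already on study formula.

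The consequence is moderate. The primary outcome, its power and the raw randomised faecal comparisons are unaffected. What is at risk is the additional baseline-adjusted analysis, the check of baseline comparability and the precision that a covariate would bring. That precision gain is 9% to 36% of the variance for rho between 0.3 and 0.6. It rests on an assumed correlation, which may well differ between the 2-month and 12-month samples and between stool variables. The contradiction does not depend on that figure.

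**What to change.** Before recruitment, align the operational sections with the synopsis and 13.3:
- 12.4: add the stool sample to the day-1 procedures, for consenting infants.
- 12.5: change the range to examination days 1 to 5. Rewrite the container procedure so that the first sample is collected after consent and before the first study feed.
- 12.7: word the stools at days 2 to 5 as following the day-1 sample.
- 12.12: mark the stool row in the 0 to <8 week column.
- 13.4: state how its rule applies to the day-1 sample. The rule requires two weeks free of infection and antibiotics and allows up to two weeks' postponement for stool as well as blood, which could push the sample past the first study feed.
- Record the date of the first study feed, so that a true pre-feeding sample can be identified.
- Analysis: use the day-1 value as an ANCOVA covariate for faecal outcomes. Section 14.1 already names ANCOVA.

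The cost is revised wording, a workable day-1 collection step and one more stool sample per consenting infant, to which the synopsis and 13.3 already commit.

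If no baseline stool is intended, correct the synopsis and 13.3 and exclude faecal outcomes from the day-1 differences in 14.3.1. That costs no samples but gives up the adjustment.

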## 2. INTRODUCTION

Breast milk is a living substance containing nutrients, hormones and other biologically active constituents which aid appropriate growth and development (Hambreus, 1977; Inch, 1996). There is clear evidence for major health benefits for both mother and baby. In infancy, breastfeeding has a protective effect, e.g. against gastrointestinal and respiratory infections, middle ear and urinary tract infections, neonatal septicaemia and NEC (Howie PW et al: Protective effect of breast feeding against infection. *Br Med J* 1990; 300:11-16; Wold AE & Adlerberth I: Breast feeding and the intestinal microflora of the infants – implications for protection against infection diseases. *Adv Exp Med Biol* 2000; 478:77-93; Pisacane A et al: Breast-feeding and urinary tract infections; *J Pediatr* 1992; 120(1):87-89; Duncan B et al: Exclusive breastfeeding for at least 4 months protects against otitis media. *Pediatrics* 1993; 95:867-872; Dewey KG et al: Differences in morbidity between breast-fed and formula-fed infants. *Pediatr* 1995; 126:696-702; Lucas A, Cole TJ: Breast milk and necrotising enterocolitis. *Lancet* 1990; 336:1519-1523).

Breast milk is known to provide advantages to the incompletely developed neonatal immunity and thus also increases active immune response to immunisation, enhancing its benefits (Hahn-Zoric M et al: Antibody responses to parenteral and oral vaccines are impaired by conventional and low-protein formulas as compared to breast-feeding. *Acta Paediatr Scand* 1990; 79:1137-1142; Pabst HF et al: Differential modulation of the immune response by breast or formula-feeding of infants. *Acta Paediatr* 1997; 86:1291-1297).

Due to important differences between the composition of breast milk and infant formulas, epidemiological evidence indicates that breastfed infants are at significantly reduced risk of infection even in industrialised societies. The protective effect of breast feeding against infectious diseases is provided by specific (antibody dependent) and broad, non-specific protective factors in human milk (oligosaccharides, proteins, glycoproteins, and lipids).

To simulate this functionality with the aim to mimic the immune-mediated beneficial effect of breast milk on morbidity and mortality of newborn infants, Numico has developed a mixture of immunologically active neutral and acidic oligosaccharides for a balanced maturation of the gastrointestinal tract and the immune system.

### 3. EXTENDED RATIONALE

Newborn babies and young infants are especially vulnerable for infectious diseases. This is mainly due to their immature GI-tract as well as based on their not yet fully developed immune system after birth. Since several years there is an increasing evidence that the cross link between the GI tract (barrier function, intestinal flora) with its effects on the epithelial cells and the underlying gut-associated lymphoid tissue (GALT) is of importance. The GALT is one of the body's largest subparts of the immune system. Due to the specific situation during the fetus development in utero the immune system of mother and child is biased to allow for growth and development of the fetus but not reacting against the immunological incompatible fetal tissue expressing both maternal and paternal antigens. This situation can be classified in a simplified manner by focussing on the specific/adaptive part of the immune system. A specific subset of the T-lymphocytes the so called T-helper cells are an important constituent of the specific immune system. The T-cells can be divided into TH1, TH2, TH3 subpopulations based on their effector functions and cytokine expression.

Bacterial and viral infections induce a TH1 dominant response and TH2 cells are involved in regulation of the IgE production as well as in inflammation and later on the bronchiolar hyper reactivity in asthma. TH3 are involved in the tolerance induction for the recognition self/non-self. Especially the balance between TH1- and TH2-helper cells can be used to classify the status of the immune system.

Newborn infants are born with a biased to TH2. This is required until birth to suppress cytolytic reactions between mother and fetus. Directly after birth the adaptive but also the innate immune system has to be further developed to prevent infection and other diseases. In healthy-born and especially breast fed infants the immune system develops to a balanced TH1 and TH2 system. Strong imbalances in direction of TH1 are associated with autoimmune diseases those in the direction of TH2 with increases incidences of atopic diseases, allergy and asthma. Especially the imbalance in direction of TH2 is relevant due to the steadily increase of atopic diseases and allergies over the last decades.

Investigations into processing of carrots showed that heating-induced softening is accompanied by changes in the solubility, size and charge density of pectin polysaccharides, as a result of  $\beta$ -eliminative degradation.

Analogue to the cooked carrot soup a pectin hydrolysate by enzymatic treatment of citrus pectin has been produced. Sodium hydroxide, pectolytic enzymes and demineralised water are used as processing aids. The quality of all raw material and processing aids meet food regulations.

The resulting citrus pectin digest has the nearly identical size and structures (degree of methylation, double bonds) as the carrot soup. The microbiological analysis of pectin hydrolysate is good.

